#### Education

This intervention component was tailored specifically for persons who have undergone a lumbar microdiscectomy. The aim of the educational session is to provide the subjects with baseline knowledge of their past and present back problem, and to discuss strategies to care for their back presently and in the future.

The development of the education program began with determining the format of the educational delivery. A "one-on-one" therapist-to-subject interaction was chosen to closely simulate the current practice pattern and promote an individualized question-and-answer format. A uniquely designed educational booklet will closely guide the one-hour educational session. The educational booklet was developed for the subject to keep.

Initially, we solicited, reviewed, and compared postoperative (microdiscectomy) instructions from the surgeons participating in this study. This information helped to guide the content of the educational booklet and it was the basis for feedback to the surgeons to guide uniformity of post surgical instructions. The booklet was divided into four sections: "Normal Anatomy of The Spine," "Anatomy of Disc Herniation and the Surgery Following It," "Strategies on How to Protect Your Back," and "Commonly Asked Questions."

During the one-hour educational session, the intervention therapist will go through the entire booklet with the subject. A 10-question multiple-choice quiz, which reviews the content of the booklet, was developed and will be administered to the subject at the completion of the educational session. Upon completion of the quiz, the intervention therapist will review the answers with the participant. There will be no specific consequences associated with performance on the quiz.

#### Exercise – USC spine exercise program

##### Trunk strength and endurance program

The trunk strength and endurance program is designed to load the trunk extensors in a graded manner, as determined by a test of their strength and endurance, by varying the angle of the trunk held against gravity. Exercise session intensity will be determined weekly and guided by test results.

There are three main features that distinguish the Strength and Endurance program from other therapeutic interventions that have been used with patients with back pain: it is goal-oriented, performance-based, and periodized. The goal of the program is for subjects to be able to hold the Sorensen test position [23] (i.e., prone/horizontal body position with spine and lower extremity joints in neutral position, arms crossed at the chest, lower extremities and pelvis supported with the upper trunk unsupported against gravity) for 180 seconds. The target hold time was chosen because it exemplified the performance of healthy adults on the Sorensen test [24,25]. There are two implied motor attributes associated with this goal. Subjects must have enough isometric back/hip extensor strength to be able to attain the Sorensen position, and enough isometric endurance to hold that position for 180 seconds. To accomplish this goal, the training program makes exclusive use of the Backstrong Spinal Rehabilitation apparatus (Backstrong LLC, Brea, CA) which, when used in conjunction with a weighted vest, allows the resistance to be progressed from very light to much heavier than the actual Sorensen test. This apparatus allows the angle of a mobile frame to vary from 75° to 0° relative to the horizontal in six increments of increasing difficulty: 75°, 60°, 45°, 30°, 15°, and 0° (Figure 2). Each angle was replaced with a level identifier (1, 2, 3, 4, 5, and 6, respectively) with Level 6 being the position of the original Sorensen test. Training on the Backstrong will be conducted on three non-consecutive days per week.

The program (Table 1) is performance-based in that subjects are to be tested weekly as part of the training, and the next week's program is determined from the previous week's test. Testing will be conducted using the procedures outlined by Flanagan and Kulig [26]. The maximum level attained during each testing session will be used to determine the training level for the following two training days. During the first half of the program, subjects will train at two levels below their maximum tested level. During the second half, they will train at one level below their maximum tested level. This procedure will allow subjects to train at an intensity that is appropriate for each individual based on their performance each week.

The program is periodized such that, after an initial two-week learning phase, subjects will alternate between phases that are designed to improve their back/hip extensor strength, and their back/hip extensor endurance, starting with a strengthening phase. The total length of the program is 12 weeks. There is also an advanced program, for those subjects who reach the goal (level 6 for 180 seconds) before the end of the 12 weeks.

During the learning phase, subjects will be taught the proper procedures for mounting and dismounting the exercise equipment, correct positioning, and testing procedures. This phase will end with a maximal test that correctly identifies the training level to begin the first strength phase.

There will be a maximum of two strength phases, each lasting a maximum of two weeks, and there will be two endurance phases, each lasting three weeks. The strength phases alternate with the endurance phases, beginning with the first strength phase. The goal of the strength phases is for the subjects to maintain the position of the original Sorensen test for at least 20 seconds. If subjects achieve this goal by the end of the first strength phase, they will not perform the second strength phase and, instead, will advance to the first endurance phase early and, then, directly to the second endurance phase after the first endurance phase.

The goal of the first endurance phase is for the subjects to be able to hold a sub-maximal position (two levels below their respective individual maximal level) for 90 seconds, while the goal of the second phase is for the subjects to be able to hold the Sorenson position (Level 6) for 180 seconds. Rest periods between repetitions of the isometric contractions will vary depending on the duration of each contraction, and will be calculated using a work-to-rest ratio (as opposed to the fixed 30-second rest in the strength phase). If the work-to-rest ratio is 1:1.5, the rest period will be calculated by multiplying the hold time by 1.5. A similar procedure will be used for work to rest ratios of 1:1 and 1:0.5. Repetitions, sets, and rest periods were designed to provide a safe progression of resistance during the intervention period.

If subjects are advanced early because they reach the particular goal of a phase, they will follow an advanced program for the remainder of the 12 weeks. This program features alternating strength and endurance phases performed at Level 6 with added resistance via a weighted vest (progressing from 5–20% of a patient's body weight). For each subject, the program ends on the 35^th ^training day with the modified Sorensen test, regardless of the point in the program at which the subject might be.

##### Mat and upright program

The purpose of the Mat and Upright Therapeutic Exercise program is to develop sound and individualized strategies to progressively and dynamically develop strength, endurance, and control of movement by the trunk and lower extremity musculature. The systematic and individualized progression and/or regression of exercise intensity is unique to this protocol and mimics the clinical decision-making process employed by physical therapists.

Three categories of exercises were selected to focus on the abdominal, back, and lower extremity musculature. A progression of these exercises of increasing difficulty was established (Table 2). The exercises are divided into three categories based on performance in supine, quadruped, and standing positions. Examples of the easiest and most challenging exercises are presented in Figures 3, 4, and 5, respectively. The exercise selection was guided by literature review [27-29], clinician expertise input via focus group discussions, and field testing. Repetitions, sets, and rest periods were further determined based on muscle endurance training principles set by the American College of Sports Medicine [30]. Each category of exercise has multiple training levels designed to accommodate subjects of varying levels of fitness and symptoms, and to allow for progression of the workload over the 12-week training period. Subjects will perform exercises from all three categories during the entire intervention period, but the level of difficulty of exercises at any point during the period may vary among the exercise categories.

A testing procedure was developed to determine the appropriate initial training level for each category of exercise. Test performance will be based upon each subject's symptoms, technique, and rate of perceived exertion. The tests will be repeated at three-week intervals during the 12-week intervention. Results will be used for data collection and to modify training levels.

Exercise performance was also evaluated to allow for progression, regression, or maintenance of exercise within each category on a weekly basis. Once a training goal is met two sessions in a row, the subject will progress to the next training level. If a subject fails to complete one-half of the target reps, hold times, or sets, or is symptom-limited for two consecutive sessions, the subject will be regressed by one level. This allows for an individualized program based on symptoms, fatigue, and ability to perform the exercise correctly.

### Outcome measures

We have used the International Classification of Functioning (ICF) conceptual framework [31,32] to classify the study's outcome measures (Figure 6). The ICF framework categories (body functions and structures, activity, participation) correspond, respectively, to Nagi's disablement model [32,33] categories (impairments, functional limitation, disability). We divided the outcome measures into primary and secondary variables. The primary outcome measures will provide an assessment of the intervention and the secondary outcome measures are descriptive, informing, and hypothesis-building. Testing of all outcome measures will be administered at the post-surgical/pre-intervention assessment, post-intervention assessment, and 1-year post-surgical assessment. In addition, completion of questionnaires and pain visual analog scales (VASs) will occur every six months after the 1-year post-surgical assessment, for the remaining four years of the study.

The subject must complete all sections of each questionnaire for the questionnaire to be considered valid. Research personnel will ensure that all sections are completed during each assessment. Incomplete questionnaires will not be accepted for data entry.

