#### Primary outcome measures

The following survey instruments were placed in the "participation" category of the ICF: Oswestry Disability Questionnaire (OD), Roland-Morris Disability Questionnaire (RM), SF-36^® ^quality of life assessment, and Subjective Quality of Life Scale (SQOL).

The OD measures the activities of daily living most likely to be limited in people with lower back pain. The most recent version of the OD will be used, in which the question regarding sex has been replaced with one regarding employment and homemaking [34]. The RM is a short questionnaire that assesses functional intolerances related to low back pain. It is easy to administer and has been shown to be reliable [35,36] Both the OD and the RM have been used as outcome measures with patients who have undergone microdiscectomy [7,9-11,37-39].

The SF-36^® ^has been used with a variety of populations to compare the effects of different diseases and treatments, and for screening individuals' health profiles [40]. For the purposes of this study, the SF-36^® ^will be used to assess baseline quality of life for each subject before and after the intervention period. It has been used in patients with low back pain and after lumbar surgeries [37]. The SQOL [41] comprises only one item, and is used to obtain a general quality of life assessment.

The "activity" primary outcome measures will include the 50-foot Walk and Repeated Sit-to-Stand tests. The 50-foot Walk test measures the time it takes to walk a distance of 50 feet as fast as tolerated. The Repeated Sit-to-Stand test measures the time it takes to complete five consecutive repetitions of a sit-to-stand sequence as fast as tolerated. Good-to-excellent test-retest reliability has been established for these measures (ICC = 0.99 and 0.89, respectively) [42].

The "body functions and structures" (i.e., "physical") primary outcome measures will include a Modified Sorenson test and pain visual analog scales [43] (VASs). The pain VASs will be administered immediately after sitting for 10 minutes and after the 5-minute Walk test.

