### Follow-up period

All of the previously described questionnaires will be administered during face-to-face evaluation sessions occurring four to six weeks after surgery, at the end of the intervention period, and one year after the surgery. They will be administered via the regular mail during the follow-up period (every six months thereafter for the next four years). The mailings will be preceded by phone calls from the study coordinators during which the subjects will be asked questions regarding their symptoms and activity level. If the subjects report that they are symptomatic, then the following questionnaires will be sent: OD, RM, SF-36^®^, SQOL, FABQ, and PAS. In this case, subjects will also receive the pain VAS forms for sitting and walking, and will be asked to report their typical symptoms (intensity and location) during these activities, but they will not need to mark the pain VAS forms immediately after sitting or walking for a certain time. If, however, the subjects report that they are asymptomatic at the time of the follow-up call, only the PAS will be sent.

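### Questionnaires with an unanswered section are refused data entry, and the completeness safeguard has no described counterpart for the eight mailed follow-up waves

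*Protocol article*

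**What the plan says.** The Outcome measures section of the protocol article sets an all-or-nothing rule: "The subject must complete all sections of each questionnaire for the questionnaire to be considered valid". The safeguard follows, "Research personnel will ensure that all sections are completed during each assessment", and then the consequence: "Incomplete questionnaires will not be accepted for data entry". No exception is made for mailed forms and no partial scoring is described.

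Under Primary outcome measures, the questionnaires concerned are the "Oswestry Disability Questionnaire (OD), Roland-Morris Disability Questionnaire (RM), SF-36" and the Subjective Quality of Life Scale (SQOL). The last of these "comprises only one item, and is used to obtain a general quality of life assessment".

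The Follow-up period section places three administrations in "face-to-face evaluation sessions occurring four to six weeks after surgery, at the end of the intervention period, and one year after the surgery". For the later waves, at six-month intervals over four more years, it says of the questionnaires: "They will be administered via the regular mail during the follow-up period". A coordinator telephones before each mailing. Participants who report symptoms are sent the full set; those who report none are sent only the Physical Activity Scale. No check or call-back after a form is returned is described, and none is ruled out.

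**The concern.** This is a stated rule, not a detail left to an analysis plan. It acts at data entry, so the answered sections of a partly completed form never reach the database. A later analysis plan could not score, prorate or impute from them without going back to the paper.

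The safeguard and the schedule do not fit together. Staff can see to completion while a participant is in the room, but at a mailed wave nobody is present during the assessment, and the only contact described comes before the form is sent. The refusal rule therefore bites mainly in the long-term phase, and the Background section gives long-term outcome as one of the two purposes of the study.

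At stake are observed answers on three primary outcomes. One blank section removes the whole form, including, for the SF-36, answers on domains unrelated to the blank. The Data analysis section plans a repeated-measures MANOVA. If that is run on complete cases, one refused form can also take the participant out of the long-term analysis. The 30% attrition allowance under Sample size lists program length, loss or increase of symptoms and second surgery as causes; refused forms are not among them.

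**Working it through.** **Plan's own figure.** The documents give no rate of incomplete questionnaires, so there is no stated figure on this point to reproduce. The sample size of about 50 per group cannot be derived from its inputs either, because no outcome, SD or control value is given. It is used only for scale in step 5.

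**Step 1: exposed waves.** Follow-up assessments run every six months from 1 to 5 years after surgery. The 1-year visit is face to face, so the mailed waves are at 1.5, 2, 2.5, 3, 3.5, 4, 4.5 and 5 years: 8 waves. With the 3 face-to-face assessments the total is 11, so 8 of 11 lack a described safeguard.

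**Step 2: exposed primary questionnaires.** Four are listed. The SQOL has one item and cannot be partly complete, which leaves 3. The maximum exposure is 3 × 8 = 24 forms, reached only by a participant who reports symptoms at all eight calls.

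**Step 3: chance of full usability.** Let q be the assumed probability that a mailed form has an unanswered section, independent across forms and waves. The probability that one questionnaire is usable at all 8 waves is (1 − q)^8; for all three it is (1 − q)^24.

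| q (assumed) | One questionnaire, 8 waves | All three, 24 forms | Expected forms refused, 24q |
|---|---|---|---|
| 2% | 0.98^8 = 0.85 | 0.98^24 = 0.62 | 0.48 |
| 5% | 0.95^8 = 0.66 | 0.95^24 = 0.29 | 1.2 |
| 10% | 0.90^8 = 0.43 | 0.90^24 = 0.08 | 2.4 |

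The share of forms lost is only q. The steep figures arise when a complete set is required across waves.

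**Step 4: fewer mailings.** A participant who is symptomatic at 4 of the 8 calls has 4 exposed forms per questionnaire and 12 in all. The probabilities become 0.98^4 = 0.92, 0.95^4 = 0.81 and 0.90^4 = 0.66 for one questionnaire, and 0.98^12 = 0.78, 0.95^12 = 0.54 and 0.90^12 = 0.28 for all three. At a given q, the table in step 3 therefore shows the largest exposure.

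**Step 5: a single comparison, for scale.** After 30% attrition, 50 × 0.7 = 35 per arm are evaluable. At two-sided alpha 0.05 (sidedness is not stated) and power 0.80, the detectable standardised difference is (1.960 + 0.842) × √(2/35) = 0.67. With a further fraction q of forms refused, n = 35(1 − q) and power ≈ Φ(0.67 × √(n/2) − 1.96):

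| q (assumed) | n per arm | Power |
|---|---|---|
| 0 | 35.0 | 80% |
| 2% | 34.3 | 79% |
| 5% | 33.3 | 78% |
| 10% | 31.5 | 76% |
| 20% | 28.0 | 71% |

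At any single time point the cost in power is modest. This step ignores the symptomatic-only mailing, which reduces n at the mailed waves for a different reason.

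**The case against.** The strongest defence is that the rule is a quality gate. Staff are told to secure completion at each assessment, mail is not excepted, and coordinators already telephone around each mailing. An operating manual may contain a call-back procedure that a condensed article omits. This stands in part. A reader might infer that incomplete mailed forms cannot be prevented or that their answers are permanently lost, but the documents say neither. They describe no call-back and do not forbid one, and a form that is not entered has not been destroyed. Even so, a mailed form whose gaps are not resolved is still refused.

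A reader might also spread the loss over all 11 assessments and four questionnaires. That would count three supervised visits and a one-item scale, and would overlook that only symptomatic participants are sent the primary questionnaires.

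Two further inferences go too far. First, skipping might be thought to bias the result because an employment section does not apply to people off work. The Oswestry question described covers homemaking as well as employment, and no evidence of selective skipping is given; bias is possible but not shown. Second, the MANOVA might be said to delete every participant with a refused form. Complete-case deletion is usual for that method, but the article states neither that nor which waves enter the model. If all waves were analysed on complete cases, the symptomatic-only mailing would already remove anyone not sent the forms at some wave. That is a separate and probably larger source of missing data.

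**Conclusion.** The point holds for the mailed follow-up only. As written, the rule discards observed Oswestry, Roland-Morris and SF-36 answers at the eight waves from 1.5 to 5 years, where its stated safeguard has no described counterpart. The immediate-effect and 1-year comparisons are largely protected, and the 50-foot Walk, Repeated Sit-to-Stand and Modified Sorensen tests lie outside the rule.

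The direction is certain, since refusing a partly answered form can only lose information. The size is not known. The usable shares of 85%, 66% and 43% for one questionnaire, and 62%, 29% and 8% for all three, rest on assumed rates of 2%, 5% and 10%, on independence, and on mailing at every wave. Fewer mailings, or skipping concentrated in the same people, would leave more participants fully usable. The further loss of whole participants depends on a complete-case MANOVA, which is likely but not stated. Long-term primary data are lost needlessly, but the trial is not invalidated and no stated figure is contradicted.

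**What to change.** In the Outcome measures section, delete the refusal rule and state instead that:

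- every returned questionnaire is entered at item level;
- coordinators, who already telephone participants before each mailing, also call back to retrieve skipped items on returned forms;
- partly completed forms are scored by each instrument's own missing-item rule, or by a proration threshold fixed in advance;
- where a form still cannot be scored, only that score is set to missing, and the participant's other data are kept;
- scoring restricted to fully completed forms is reported as a sensitivity analysis.

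The instruments' missing-item rules are not in the documents, so the sponsor must check them before citing them. The analysis section should also say how participants with some missing scores are handled in the repeated-measures analysis.

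The cost is a wording change, slightly more data entry, some extra telephone calls and a little added measurement error in prorated scores.

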#### Primary outcome measures

The following survey instruments were placed in the "participation" category of the ICF: Oswestry Disability Questionnaire (OD), Roland-Morris Disability Questionnaire (RM), SF-36^® ^quality of life assessment, and Subjective Quality of Life Scale (SQOL).

The OD measures the activities of daily living most likely to be limited in people with lower back pain. The most recent version of the OD will be used, in which the question regarding sex has been replaced with one regarding employment and homemaking [34]. The RM is a short questionnaire that assesses functional intolerances related to low back pain. It is easy to administer and has been shown to be reliable [35,36] Both the OD and the RM have been used as outcome measures with patients who have undergone microdiscectomy [7,9-11,37-39].

The SF-36^® ^has been used with a variety of populations to compare the effects of different diseases and treatments, and for screening individuals' health profiles [40]. For the purposes of this study, the SF-36^® ^will be used to assess baseline quality of life for each subject before and after the intervention period. It has been used in patients with low back pain and after lumbar surgeries [37]. The SQOL [41] comprises only one item, and is used to obtain a general quality of life assessment.

The "activity" primary outcome measures will include the 50-foot Walk and Repeated Sit-to-Stand tests. The 50-foot Walk test measures the time it takes to walk a distance of 50 feet as fast as tolerated. The Repeated Sit-to-Stand test measures the time it takes to complete five consecutive repetitions of a sit-to-stand sequence as fast as tolerated. Good-to-excellent test-retest reliability has been established for these measures (ICC = 0.99 and 0.89, respectively) [42].

The "body functions and structures" (i.e., "physical") primary outcome measures will include a Modified Sorenson test and pain visual analog scales [43] (VASs). The pain VASs will be administered immediately after sitting for 10 minutes and after the 5-minute Walk test.

The Modified Sorensen test was derived from Biering-Sorensen [23], who used this test to assess the isometric strength and endurance of the lumbar back extensors in individuals with low back pain. The purpose of the Modified Sorensen test in our study is to assess the isometric strength and endurance of the lumbar musculature of each subject. The Sorensen test was shown to be reliable when used to test subjects who had a history of current or previous episodes of lower back pain [24,42]. In addition, the test was determined to be clinically useful because it was easy to perform, required minimal equipment, and had the most support in the literature [19,24,42,44]. Finally, the Sorensen test was found not to be linked to genetic attributes of strength, and therefore is more suitable for a rehabilitative outcome measure [45].

